#### Implementation outcomes

Implementation outcomes will be assessed across five domains (see table 2). Reach will be measured by the number, proportion and representativeness of Aboriginal and Torres Strait Islander participants, including demographic characteristics and current access and use of Aboriginal health services, obtained from baseline participant surveys. Adoption will be measured by the number, proportion and representativeness of participants who complete all baseline and follow-up assessments and uptake of intervention components, including *Quit Pack* resources and NRT, phone calls with *Which Way?* team members and participation in the online forum. These data will be obtained from trial tracking systems, including data kept by the research team on NRT pack requests, behavioural supports provided and the number of posts on the online forum. Implementation will be measured by assessing contextual adaptations made to the intervention recorded via the community researchers’ project implementation logs and weekly project meetings. Weekly project meetings will follow a structured format guided by three key questions: (1) what worked well, (2) what has not worked well and (3) what changes are needed to improve delivery. These discussions will focus on fidelity to intervention protocols, quality and consistency of delivery and contextual factors influencing implementation. For this trial, maintenance outcomes have been conceptualised to include individual-level cessation outcomes, reflecting the importance of sustained abstinence and ongoing quit attempts as key indicators of long-term intervention impact in smoking and vaping cessation.^41^ Maintenance will therefore be determined by prolonged cessation and quit attempts at 12-month follow-up, as well as an assessment of the cost-effectiveness of the intervention as an indicator of programme-level sustainability, as found appropriate in a previous work.^27^

**Table 2 T2:** Summary of effectiveness and implementation outcome measures

Dimension	Outcome	Data collection source Analysis plan	Data collection time points
**Reach** Determine the extent to which the *Which Way? Quit Pack* intervention reaches the target population of Aboriginal and Torres Strait Islander people who smoke daily and/or vape daily*.*	Number of participants enrolled in the trial.	Participant survey Quantitative analysis	Baseline
	Participant representativeness including age, gender, geographical location, remoteness classification (using the Socio-Economic Indexes for Areas (SEIFA)) and current access and use of Aboriginal health services.	Participant survey Quantitative analysis	Baseline
**Effectiveness** Determine the impact of the *Which Way? Quit Pack* intervention on smoking and vaping cessation rates at 3, 6 and 12-month follow-ups, with a primary focus on abstinence at 12 months.	Self-reported 7-day prevalence abstinence.	Participant survey Quantitative analysis	3, 6 and 12 months post-baseline
	Prolonged abstinence.	Participant survey Quantitative analysis	3, 6 and 12 months post-baseline
	Number of quit attempts lasting ≥24 hours.	Participant survey Quantitative analysis	3, 6 and 12 months post-baseline
	Biochemical verification of smoking status.	Carbon monoxide via Smokerlyzer Quantitative analysis	3, 6 and 12 months post-baseline
**Adoption** Determine the extent to which participants use each component of the *Which Way? Quit Pack* intervention*.*	Absolute number and proportion of participants who complete each survey.	Participant survey Quantitative analysis	Baseline and 3, 6 and 12 months post-baseline
	Representativeness (age, gender, geographical location, remoteness classification (using SEIFA)) of participants who complete each survey.	Participant survey Quantitative analysis	Baseline and 3, 6 and 12 months post-baseline
	Uptake and frequency of use of intervention components including nicotine replacement therapy (NRT), phone-based behavioural counselling and participation in the online forum.	Data from trial tracking systems (NRT pack requests, behavioural support records and online forum use) Quantitative analysis	Baseline to end of intervention (3-month follow-up)
**Implementation** Determine the fidelity, quality and consistency of the *Which Way? Quit Pack* intervention delivery, as well as the barriers and facilitators encountered during the implementation process*.*	Qualitative process evaluation using staff feedback to assess fidelity, barriers and facilitators to delivery. Evaluation will be guided by three questions: (1) ‘what worked well?’ to identify effective strategies, resources or processes supporting implementation; (2) ‘what has not worked well?’ to explore challenges, barriers or gaps experienced; and (3) ‘what changes need to be made?’ to gather suggestions for addressing barriers and improving implementation.	Implementation review meetings with project staff Qualitative analysis	Weekly
**Maintenance** Determine the long-term sustainability of the *Quit Pack* intervention on smoking and vaping cessation at 12-month follow-up and conduct a health economic evaluation to inform scalability and sustainability of the intervention for continued use and support within the community and healthcare settings beyond the study period.	Self-reported 7-day point prevalence abstinence at 12-month follow-up.	Participant survey Quantitative analysis	12 months post-baseline
	Prolonged abstinence at 12-month follow-up.	Participant survey Quantitative analysis	3, 6 and 12 months post-baseline
	Optional biochemical verification of smoking status at 12-month follow-up.	Participant survey Quantitative analysis	12 months post-baseline
	Cost-effectiveness of the intervention including cost per participant, health-adjusted life years gained, hospitalisations averted and number of quitters.	Participant surveys using Short-Form 8 Health Survey (SF-8D) Quantitative analysis	Baseline and 3, 6 and 12 months post-baseline

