### Study aims

Building on this platform of community leadership, partnership governance, iterative knowledge translation and our completed work,^25
27^ this study aims to evaluate both the implementation and effectiveness of the culturally grounded *Which Way? Quit Pack* smoking and vaping cessation intervention, developed by and for Aboriginal and Torres Strait Islander people, nationally using a single-group hybrid type 2 effectiveness-implementation study. This study will use the Reach-Effectiveness-Adoption-Implementation-Maintenance (RE-AIM) framework^28^ to evaluate the following outcomes:

*Effectiveness outcomes:* the primary outcome is self-reported 7-day point prevalence abstinence from smoking and/or vaping at 12-month follow-up. Secondary outcomes include: (1) self-reported 7-day point prevalence abstinence from smoking and/or vaping at 3 and 6 months; (2) prolonged abstinence, defined as no smoking or vaping from 1 month after receipt of the *Which Way? Quit Pack*, allowing for lapses of up to 7 consecutive days; (3) number of quit attempts lasting longer than 24 hours at 3 and 6-month follow-ups; and (4) biochemical verification of smoking status using expired carbon monoxide (CO) breath test at 3, 6 and 12-month follow-ups.*Implementation outcomes:* implementation outcomes will include: (1) intervention reach, including participation rates and representativeness of Aboriginal and Torres Strait Islander participants across geographical areas; (2) intervention adoption, including the number and proportion of participants completing baseline and all follow-up assessments at 3, 6 and 12 months, and uptake and use of intervention components; (3) implementation, including intervention acceptability, feasibility and fidelity; and (4) maintenance, including smoking and vaping abstinence at 12-month follow-up as a proxy for sustained behaviour change, and health economic evaluation of costs and potential scalability assessed using the Short-Form 8 Health Survey (SF-8D) at baseline and 3, 6 and 12 months.

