#### Mailed quit pack, inclusive of NRT

Participants who enrol in *Which Way? Quit Pack* will receive a comprehensive mailed smoking cessation intervention delivered to their nominated postal address. Each *Quit Pack* will include: (1) merchandise from Aboriginal-led, majority Aboriginal-owned accredited social enterprise ‘Clothing the Gaps’ to celebrate pride in culture; (2) a written health education story book developed specifically by the Indigenous *Which Way?* team that offers culturally relevant advice and guidance on quitting and NRT use; (3) an iCOquit Smokerlyzer (for those who report using tobacco only), which is a handheld device that measures CO levels in exhaled breath, supporting self-monitoring and motivation; and (4) a maximum 12-week supply of NRT (see table 1). The *Quit Pack* box and its presentation also embed culturally relevant, engaging and visually meaningful elements throughout, creating an experience that reflects and celebrates Aboriginal and Torres Strait Islander cultures and supports participants to feel culturally represented and safe when receiving and engaging with the intervention. Participants will receive NRT in two separate mailouts. The first will be sent at baseline and will include an 8-week supply of NRT. Six weeks post-enrolment into the intervention, participants will receive an SMS or email (as per their selected preference) asking them to confirm if they wish to receive the further 4-week supply. On confirmation, the second shipment will be mailed (see figure 2). NRT is available over the counter in Australia and does not require a prescription for use.

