### Statistical analysis

The representativeness of the sample will be assessed by comparing observed proportions to expected proportions derived from Australian Bureau of Statistics population data using χ^2^ goodness-of-fit tests. The RE-AIM quantitative components will be described as counts and percentages with 95% CIs, and qualitative components will be thematically analysed (see table 2). Associations between participant demographic characteristics and quit rates will also be estimated using logistic regression models, as secondary exploratory analyses. Causal machine learning models^31^ will be used to assess potential heterogeneity in effectiveness of implementation strategies by participant subgroups. An ITT analysis will be performed for all effectiveness cessation outcomes, where participants with missing smoking or vaping cessation outcomes are classified as smokers or vapers. Multiple imputation using chained equations will be used to classify all remaining missing outcomes, as well as missing data on confounders. Attrition will be reported in the participant flow chart, and the baseline demographic and smoking/vaping characteristics of completers and non-completers will be compared via t-tests and χ^2^ tests as appropriate. Complete case results will also be reported to provide transparency and allow comparison across analytical methods.^42^ The proportion of participants with a quit attempt longer than 24 hours will be estimated within the subgroup of participants who have not been continuously abstinent at the 3, 6 and 12-month follow-ups.

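### Table 2 classifies remoteness with a socio-economic index in both the Reach and Adoption rows, so that one variable does not measure remoteness

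*Protocol article*

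**What the plan says.** The Study aims section of the protocol article puts reach first among the implementation outcomes and describes it as "participation rates and representativeness of Aboriginal and Torres Strait Islander participants across geographical areas". Table 2, under Implementation outcomes, turns this into variables.

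- **Reach row:** "Participant representativeness including age, gender, geographical location, remoteness classification", with the last item specified as "remoteness classification (using the Socio-Economic Indexes for Areas (SEIFA". Access to and use of Aboriginal health services completes the list. The source is the baseline participant survey.
- **Adoption row:** "Representativeness (age, gender, geographical location, remoteness classification (using SEIFA)) of participants who complete each survey". The source is the participant survey at baseline and at 3, 6 and 12 months.

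The Statistical analysis section then assesses representativeness by "comparing observed proportions to expected proportions derived from Australian Bureau of Statistics population data", using goodness-of-fit tests. The section on the mailed pack says that it is "delivered to their nominated postal address", so the study holds an address for each participant.

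**The concern.** The construct and the instrument do not match. Remoteness concerns where a place lies relative to population centres and services. A socio-economic index ranks areas by social and economic conditions. The two may be correlated, but one cannot stand in for the other: areas with the same socio-economic rank can lie in a city or far from one.

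This is more than untidy labelling. The programme is delivered by mail in all states and territories and is meant to inform sustainable national implementation. Whether people in remote places enrol, and whether they stay in follow-up, is a natural question for the users of the results. A table headed remoteness but filled with socio-economic strata would give them a misleading answer under a plausible label. The same applies to the Adoption table, which describes who completes each survey.

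**Working it through.** No arithmetic is needed to establish the mismatch. It follows from setting the relevant places side by side.

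1. **What is to be measured.** Both rows name remoteness classification as an item.
2. **With what.** The Reach row names the index and spells out its acronym; the Adoption row has "remoteness classification (using SEIFA". The full name in the Reach row identifies the index as socio-economic, so no outside source is needed to see the mismatch.
3. **Is it a slip in one cell?** The same pairing appears in two rows under two different domains. It therefore has to be read as the stated specification.
4. **Is it corrected elsewhere?** No remoteness or accessibility classification is named in the Study aims, the Implementation outcomes text, the Statistical analysis section or any other row of Table 2. Nor is a separate socio-economic variable listed in the two rows. If the authors meant two items, remoteness and socio-economic position, the table has merged them into one.
5. **What follows if the plan is applied literally.** The observed proportions by remoteness would be proportions by socio-economic stratum. The expected proportions taken from Australian Bureau of Statistics data would either be on the same socio-economic strata, and so answer a different question, or be on a true remoteness scale, and so not match the observed categories.
6. **How much of the assessment is touched.** The Reach row lists age, gender, geographical location, remoteness, and access to and use of Aboriginal health services: one item of five is affected. The Adoption row lists age, gender, geographical location and remoteness: one item of four is affected.
7. **Is the information lost?** Not necessarily. Geographical location is listed separately in both rows, and a postal address is held. If location is kept at postcode or small-area level, a remoteness category can be attached to each participant afterwards. If it is kept only as state or territory, the survey item would not be enough. The article does not give the level.

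**The case against.** The strongest reply is that little is at stake. The stated aim is "representativeness of Aboriginal and Torres Strait Islander participants across geographical areas", and the geographical-location item serves that aim directly whatever happens to the remoteness item. The aim itself does not mention remoteness. The affected variable is one descriptive item, no hypothesis depends on it, and the remedy is a few words.

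Most of this stands, and it sets the limits of the point. A reader might infer from Table 2 that Reach and Adoption cannot show at all whether remote communities were reached. The documents do not support that. Location is recorded as its own item, an address exists for each participant, and remoteness may be recoverable from either. The stronger consequence would largely hold only if location were kept no finer than state or territory, and the article does not say so.

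The reply does not remove the error itself. The article is not merely silent on a detail that a fuller protocol or a statistical analysis plan could supply. It names an instrument, twice, and that instrument measures something else.

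**Conclusion.** The point holds in a limited form. As specified, the remoteness variable in the Reach and Adoption rows measures area socio-economic position, so the remoteness part of the representativeness assessment is mis-specified. The geographical-location item, the other representativeness items, the primary outcome of 7-day abstinence at 12 months and the sample size of 2000 are unaffected.

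The conclusion rests on reading the index as its full name describes it, and on the article naming no other remoteness measure. That the remedy is cheap rests on a further assumption: that location is recorded at postcode or small-area level.

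A reader might go on to fault the rest of the representativeness analysis, but the text does not support this. The Statistical analysis section does not say that the reference figures are for the general population; it leaves the reference table open, which an article may do. Nor does it rely on goodness-of-fit p-values alone, since it also reports the quantitative RE-AIM components as percentages with 95% confidence intervals.

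The correction should be made, but it does not threaten the trial's main conclusions.

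**What to change.** In both the Reach and the Adoption rows of Table 2:

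- Replace the socio-economic index with a recognised geographic remoteness classification, named explicitly and derived from the participant's recorded location or postcode.
- If area socio-economic position is also of interest, list the index as a separate item under that name.

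In the Statistical analysis section, take the expected proportions for remoteness from reference data on the same remoteness categories.

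State the level at which geographical location is recorded, and keep it at postcode or small-area level. If the postal address is used instead, say so, because a nominated mailing address need not be the place of residence.

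The cost is a few words in two rows and one extra lookup. No new data item is needed if postcode is already kept. If it is not, one survey field has to be added, which is easiest before data collection opens on 29 May 2026. No outcome, sample-size or effectiveness analysis changes.

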### Sample size

A sample size of 2000 eligible consenting participants will enable the study to estimate the primary effectiveness outcome proportions and 95% CIs with a margin of error between 0.8% and 2% for proportions that range between 5% and 50% (and by symmetry as high as 95%). Assuming a minimum 12-month cessation 7-day point prevalence of 5%, this sample size will give the study over 80% power to detect differences in the secondary outcomes. We will use a type 1 error rate of 5%. Pilot data indicated potential 7-day point prevalence at 3 and 6 months of 23% and 16%.^25^

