In direct response to community-identified priorities, the *Which Way? Quit Pack* intervention was codesigned in 2021 in genuine partnership with peak organisations including the Aboriginal Health & Medical Research Council (AH&MRC), Quit Victoria and the Victorian Aboriginal Community Controlled Health Organisation (VACCHO).^23^ The initial *Quit Pack* intervention aimed to answer the community-led question, ‘what supports our mob to quit smoking?’, by examining the feasibility and acceptability of a mailed smoking cessation package and the uptake of a range of different behavioural and pharmacological supports. *Quit Pack* contained mailed smoking and vaping cessation support including written cessation resources, proactive referral to Quitline, mobile phone applications and the option of free combination NRT.^23^ At the time of intervention development, existing evidence suggested that interest in and uptake of NRT were low among Aboriginal and Torres Strait Islander people.^24^ However, the pilot demonstrated strong interest from Aboriginal and Torres Strait Islander people, recruiting 165 participants in 3 months (exceeding the target of 100), high uptake of NRT (>90% of participants accepted and used NRT) and achieving 7-day self-reported point prevalence smoking abstinence at 6 months of 34% (complete case) and 19.4% (intention to treat (ITT)), respectively.^25^ Building on this success and continued interest from Aboriginal and Torres Strait Islander people for mailed cessation supports, a subsequent hybrid type 1 effectiveness-implementation study was codeveloped with the established and sustained community partnerships conducted across New South Wales (NSW), Australian Capital Territory and Victoria in 2023–2024.^26^ The effectiveness-implementation trial recruited 722 participants in 9 months and achieved 7-day self-reported abstinence rates of 39% at 6-month follow-up and 44% at 3 months (complete case).

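### The lower 95% margin of error in the sample-size paragraph is misstated (0.8% should be 0.96%), and the adjacent power claim names no difference and cannot be checked

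*Protocol article*

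**What the plan says.** The Sample size section of the protocol article justifies 2000 participants in two steps.

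The first is precision. It promises 95% confidence intervals for the primary outcome, "with a margin of error between 0.8% and 2% for proportions that range between 5% and 50"%. The confidence level is stated, and the range is said to extend by symmetry to 95%.

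The second is power. Starting from a stated floor ("Assuming a minimum 12-month cessation 7-day point prevalence of 5"%), the section says that "this sample size will give the study over 80% power to detect differences in the secondary outcomes", and adds "We will use a type 1 error rate of 5"%. It then gives background rates: "Pilot data indicated potential 7-day point prevalence at 3 and 6 months of 23% and 16"%.

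Three other places bear on the reading:

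- Statistical analysis counts participants with missing cessation outcomes as still smoking or vaping, so the denominator for the primary outcome stays at 2000.
- Study aims lists the secondary outcomes: abstinence at 3 and 6 months, prolonged abstinence, quit attempts, and carbon monoxide verification.
- The strengths and limitations box and the Discussion both say that there is no comparison arm.

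**The concern.** In a single-group estimation study, the width of the confidence interval is the main justification for the sample size. All the inputs to that width are stated (n, confidence level, proportions), so the printed margin should follow from them. At the lower end it does not.

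The power sentence has the opposite problem: it states a result without the inputs that would produce it. With one group, a difference could mean a change between time points, a contrast between participant groups, or a departure from a fixed value. Each gives a different answer. A reader who accepts more than 80% power as a general property of the study could read too much into a later null comparison.

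**Working it through.** **Inputs.** From the Sample size section: n = 2000, 95% confidence, proportions of 5% and 50%, type 1 error 5%, assumed 12-month abstinence of at least 5%. Sidedness is not stated; two-sided is taken, to match a 95% interval.

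**Step 1: try to reproduce the stated margins.** Wald half-width = z × √(p(1 − p)/n).

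- p = 5%: √(0.05 × 0.95/2000) = 0.004873. Times 1.960 = 0.00955, or 0.96%. Stated: 0.8%.
- p = 50%: √(0.5 × 0.5/2000) = 0.011180. Times 1.960 = 0.02191, or 2.19%. Stated: 2%.

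The upper figure is reproduced if 2.19% is rounded to a whole percent. The lower is not, because 0.955% does not round to 0.8%.

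**Step 2: try other 95% methods.**

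| Method (95%, n = 2000) | p = 5% | p = 50% |
|---|---|---|
| Wald | 0.955% | 2.191% |
| Wilson | 0.958% | 2.189% |
| Clopper-Pearson (half-width) | 0.981% | 2.215% |
| Continuity-corrected | 0.980% | 2.216% |

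None gives 0.8% at p = 5%.

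**Step 3: what would give 0.8%?** The implied multiplier is 0.008/0.004873 = 1.642, close to the 1.645 of a 90% interval. At 90% the half-widths are 1.645 × 0.004873 = 0.80% and 1.645 × 0.011180 = 1.84%. At 95%, a margin of 0.8% at p = 5% would need 1.960² × 0.0475/0.008² ≈ 2,851 participants, and a margin of exactly 2.0% at p = 50% would need 1.960² × 0.25/0.02² ≈ 2,401.

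**Step 4: could something else explain it?** Attrition cannot: the denominator stays at 2000, and losing participants would widen the interval. A finite-population correction would narrow it, but none is mentioned. To bring 0.955% down to a figure that rounds to 0.8%, the target population would have to be only about 5,200 to 9,600 people.

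**Step 5: the power sentence.** There is no stated figure to reproduce beyond the 80% itself. For illustration only, assume two independent groups of 1000, a rate of 5% in one, and a two-sided 5% test of two proportions with pooled variance under the null:

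Power = Φ[(d − 1.960 × √(2p̄(1 − p̄)/1000)) / √((p₁(1 − p₁) + p₂(1 − p₂))/1000)], where d = p₂ − p₁ and p̄ is the mean of the two rates.

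- 5% v 7%: (0.020 − 0.0208)/0.0106 = −0.08, power 47%.
- 5% v 8%: power 78%.
- 5% v 8.1%: (0.031 − 0.0217)/0.0110 = 0.84, power 80%.
- 5% v 9%: power 94%.

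Other equally unstated comparisons give other answers. A one-sample test of all 2000 against 5% has 79% power at a true rate of 6.4% and 84% at 6.5%. Two independent groups of 1000 at 16% and 23% would give about 98%.

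**The case against.** The best defence is that the consequences are slight. The study estimates proportions in one group, the article sets no success threshold, and the correct margins are only 0.16 and 0.19 percentage points wider than printed. Nobody would choose a different sample size because of this. That stands, and it limits the severity. It does not make 0.8% right.

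Several stronger readings are tempting, and the document does not support them:

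- *Both ends are wrong because a 90% interval was used.* The numerical match at 0.8% is close, but the document does not say so. The upper end does not settle it: 2.19% and 1.84% both round to 2%. Only the lower figure is a demonstrable error.
- *The power claim is false.* It is uncheckable, which is different. The 1000/1000 split and the 5% starting rate for one group are illustrations, not the plan's comparison. The listed secondary outcomes are not subgroup contrasts, the demographic regressions are labelled exploratory, and some choices of difference give well over 80%.
- *The pilot rates contradict each other.* The Introduction reports the pilot as "achieving 7-day self-reported point prevalence smoking abstinence at 6 months of 34% (complete case) and 19.4% (intention to treat (ITT)), respectively", while Sample size gives 16% at 6 months. The Introduction's figures are for smoking; the Sample size figure names neither product nor analysis set. Both cite the same reference, but the article also cites that reference for more than one earlier study. A conflict is possible but not established, and the 16% does not enter the margins.
- *The real margins are wider still because of dropout.* The ratio 19.4/34 suggests about 57% follow-up in the pilot, but at 6 months rather than 12, and the primary analysis keeps all 2000 in the denominator.

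It can also be said that the detail behind the power claim may sit in a fuller document. It may, but the article prints the 80% as a result, and a printed result needs the difference to which it refers.

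**Conclusion.** The lower margin is wrong as written: for a 95% interval with n = 2000 and p = 5% it is 0.96%, not 0.8%. The upper margin is 2.19%, printed as 2% by whole-percent rounding and so given to less precision than the lower one. This rests only on figures in the Sample size section and on simple random sampling without a finite-population correction, which is how that section reads.

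The power sentence is not shown to be false. It is tied to no difference, comparison or group sizes, and it cannot be true of every difference: under the assumed 1000/1000 split from 5%, anything below about 3.1 points has less than 80% power.

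Severity is minor. The sample size, the design and the analysis are unaffected.

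**What to change.** 1. Keep n = 2000 and restate the 95% margin of error as between 1.0% and 2.2% for proportions between 5% and 50%, with both ends to one decimal place.
2. State what the power claim refers to: which secondary outcome, which comparison (time points, groups or a fixed value), the size of the difference, and the group sizes if there are groups. If no specific comparison was intended, delete the sentence; the precision statement is enough for a single-group estimation study.
3. Optionally, label the product (smoking, vaping or both) and the analysis set behind the 16% in Sample size and the 19.4% in the Introduction, so that a reader can see whether they measure the same thing.

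The cost is wording only. The stated precision becomes slightly less favourable, and no participants, visits or analyses are added.
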